### Study timelines

Table 1 displays a summary of important time points in the feasibility study.

[figure not shown]

**Table 1 Tab1:**
[figure not shown]
Schedule of enrolment, intervention, and data collection: summary of key trial time points

*−*t*_*1*_ = baseline, ***t*_*1*_ = programme delivery, ****t*_*2*_ = follow-up 1 (12 weeks), *****t*_*3*_ *=* follow-up 2 (6 months)

### Data management

All personal participant information will be collected in a separate password-protected file held by the RA. Each participant will be allocated an identification code stored separate from participant responses. The RA will enter the de-identified participant responses in a purpose-built database. A codebook for the database will be developed. A sample of at least 20% percent of data will be checked by the Research Fellow. If the initial check produces an error rate above 1%, a full re-entry of data will be required. If the error rate is less than 1%, the Research Fellow will amend any errors in the final data sheet [33]. The de-identified data will be analysed by the trial team and stored securely for 10 years after which they will be destroyed. Qualitative interview audio files will be recorded on dictaphones and immediately transferred to a password-protected computer. Audio recordings will be sent to a transcriber who will sign a confidentiality agreement and transcribe the recordings verbatim. Transcripts will be stored on a password-protected computer. Salivary samples will be sent to a laboratory in the UK for analysis following the procedures set out in a salivary sample protocol. Only the trial team will have access to the trial data.

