### Objectives

The primary objectives of the trial are as follows:
(i)To determine the feasibility and acceptability of trial processes including randomisation of districts, recruitment, and data collection in both intervention and control arms(ii)To assess data quality and completion rates for the main outcome measures for a future definitive trial (DT) including biochemically validated abstinence from smoking (using salivary testing) at 12 weeks (end of programme) and 6 months (longer-term outcome)(iii)To estimate the sample size and design for a future DT including an estimate of the intra-cluster correlation coefficient (ICC) to account for the effect of ‘clustering’ in design and analysis

The secondary objectives of the trial are as follows:
(i)To test the robustness of trial design with respect to context for delivery of the intervention, implementation processes, and key mechanisms of impact, from which to optimise design of a full effectiveness trial(ii)To develop strategies to optimise recruitment and dissemination of findings to trial stakeholders to inform knowledge exchange and future research

The study protocol (version 3.0, 19 October 2018) has been developed in line with the Standard Protocol Items: Recommendations for Interventional Trials (SPIRIT) 2013 statement [16] (Additional file 1). Any changes to the protocol will be communicated to all investigators, submitted for ethical approval, and reflected in changes to the trial registry.

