### Sample size

In the previous WCQ feasibility study, two areas in Dublin were targeted with populations of 7800 and 8000, respectively. In total, 39 women signed up for the programme, evenly split between the two areas (20 in one area and 19 in the other), and of these, 29 women (74%) were retained at 12 weeks follow-up [15]. Subsequent WCQ programmes (February 2015 to April 2016) have demonstrated this retention rate was maintained at 62% (83/133) (Irish Cancer Society, personal communication). Therefore, based on this existing evidence, if 194 women (97 per arm) are recruited into the study, 120 women are predicted to be in this pilot study by 12 weeks [19]. This will be sufficient to identify potential problems in practicality/feasibility, which have a 5% probability of occurrence [20]. In the previous feasibility study [15], 50% of women who made contact were subsequently recruited to one of two 12-week programmes running concurrently in one district (morning or evening programmes), corresponding to approximately 20 women per programme. If the WCQ programme is run sequentially in 4 districts with 2 concurrent WCQ groups each time (i.e. 8 programmes), then there is potential to recruit up to 160 women during the period January 2018 to June 2019 (18 months), thus exceeding the 97 required. However, the unknown parameters, which need to be estimated from this pilot trial, are the retention rates for the usual care districts, predicted to have much lower rates. Data will also be used to estimate the intra-cluster correlation (ICC), and this data together with recruitment and attrition rates will be used to inform the sample size for the DT. A flow diagram of the study design is attached (Fig. 1). It will be conducted in keeping with the CONSORT statement extended for reporting cluster RCTs [21].

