#### Secondary outcomes

The secondary outcomes are as follows:
(i)Retention and data completion rates in each trial arm at 12 weeks and 6 months post-quit date (set in week 2) as a follow-up time point for a future DT(ii)Proportion who are continuously absent from smoking (as per Russell’s Standard) [23], at 12 weeks (primary outcome for a future DT) and at 6 months after their quit date, corroborated by salivary cotinine and anabasine(iii)Proportion of enrolled smokers who engage with smoking cessation services in each trial arm (engagement is defined as arrival for a first face-to-face appointment with a smoking cessation adviser and having set a quit date)(iv)Number of sessions attended in each trial arm(v)Proportion in each arm who report improvement in health status measured at baseline (week 1) and 12 weeks and 6 months

Data collection will be carried out at week 1, at week 12, and at 6 months post-quit date by the RA via a detailed face-to face questionnaire. Socio-demographic characteristics, smoking behaviour, quality of life (measured by the Short Form-12, Version 2 survey [24]), and health status will be recorded at week 1. Retention and data completion rates, changes in smoking behaviour, and health status will be collected at weeks 6 and 12. Salivary cotinine ± anabasine to biochemically validate self-reported smoking cessation will be recorded at week 12 and 6/12. Attendance sheets will be provided by service delivery providers. A thank you payment (€20 shopping voucher) will be provided at 12 weeks and at 6-month follow-up to encourage continued participation.

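### After a passed 20% check, entry errors in up to four fifths of the records stay undetected, including in the few fields that define validated abstinence; checking those fields in full would be a cheap improvement.

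*Protocol article*

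**What the plan says.** The Data management section describes single entry by the Research Assistant (RA): "The RA will enter the de-identified participant responses in a purpose-built database". It then sets the check: "A sample of at least 20% percent of data will be checked by the Research Fellow". Two outcomes follow. The first is "If the initial check produces an error rate above 1%, a full re-entry of data will be required". The second is "If the error rate is less than 1%, the Research Fellow will amend any errors in the final data sheet". A rate of exactly 1% falls under neither.

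The section gives no separate threshold, full check or double entry for any group of fields. It does not state the unit of sampling or the denominator of the error rate.

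Two other places bear on the point. Primary objective (ii) is "To assess data quality and completion rates for the main outcome measures" of a future definitive trial. Under Secondary outcomes, abstinence at 12 weeks is named as that trial's primary outcome, "corroborated by salivary cotinine and anabasine".

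**The concern.** A check finds errors only in the data it examines. When the sampled error rate is below 1%, the amendment step reaches at most the sampled fifth (more if the sample exceeds the 20% minimum), and the rest goes into the analysis unverified. For most questionnaire items this is an ordinary trade-off. It is less comfortable for the few entries that decide whether a woman counts as a validated quitter or as followed up, because the pilot exists to supply those figures to the definitive trial.

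A second, weaker worry concerns the threshold. If one rate is computed over the whole database, the abstinence fields are a small part of its denominator, so the rate says little about them either way.

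**Working it through.** **Inputs.** From Sample size: 194 women recruited (97 per arm), retention 62% (83/133), 120 women expected at 12 weeks. From Data management: at least 20% checked, 1% trigger. Assumed, because the article does not give them: F fields per woman, k of them abstinence fields (2 to 4), error rate e in those fields and b in all others.

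**The plan's own figure.** 194 × 0.62 = 120.3, which reproduces the stated 120 (121.1 with unrounded 83/133).

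**Records checked.** If sampling is by woman, 0.20 × 194 ≈ 39 at recruitment and 0.20 × 120 = 24 at 12 weeks. Up to 80% stay unchecked: about 155 of 194, or 96 of 120.

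**Errors left after a pass, one field, 120 records.** Expected errors are 120e, of which 20% are found and 80% remain.

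| e | wrong | found | left |
|---|---|---|---|
| 1% | 1.2 | 0.24 | 0.96 |
| 5% | 6.0 | 1.2 | 4.8 |
| 10% | 12.0 | 2.4 | 9.6 |

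**Effect of one wrong entry.** 1/97 = 1.0 percentage point in that arm. For scale, if 12 of 97 were abstinent (assumed; 12.4%), the simple 95% margin is 1.96 × √(0.124 × 0.876 / 97) ≈ 6.6 points before any allowance for clustering.

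**What a database-wide rate can hide.** Pooled rate = [k·e + (F − k)·b]/F. Setting this to 1% gives the largest e that sits at the threshold: e = [0.01F − b(F − k)]/k.

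- F = 100, b = 0: 50% (k = 2) or 25% (k = 4).
- F = 100, b = 0.5%: 25.5% or 13%.
- F = 20, b = 0: 10% or 5%.
- Errors uniform (e = b): the pooled rate equals e, so nothing is masked.

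In a simulation with 39 women checked, e = 10% and b = 0.3%, the check passes with probability 1.00 (k = 2) or 0.99 (k = 4) for F = 100, but only 0.22 or 0.003 for F = 20.

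**Would a per-field threshold on the same sample be enough?** The probability of seeing no error in a field is (1 − e)^n. At e = 2% it is 0.98^39 = 0.45 or 0.98^24 = 0.62. These misses come from sampling, not from pooling, so a per-field rule would miss just as often. At e = 5% a per-field 1% rule would trigger with probability 1 − 0.95^39 = 0.86 or 1 − 0.95^24 = 0.71. Only a full check closes the gap.

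**Cost ceiling.** 194 women × 5 fields × 2 visits = 1,940 values. It is a ceiling because not every woman is expected to be retained.

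**The case against.** The strongest reply is that a sampled check with a trigger for full re-entry is a defined procedure with a cited source, and that the article condenses a longer protocol. A codebook and a salivary sample protocol are mentioned but not shown, and either could contain checks on the outcome fields. The sample is a minimum. That the rate is pooled, and that only sampled errors are amended, is the natural reading and not literal wording. The entry sentence covers participant responses; how laboratory results and attendance sheets reach the database is not described. Saliva testing is also a partial cross-check on a woman wrongly entered as abstinent. All of this stands and limits the weight of the point. It does not remove it: the rule as published makes no exception for the outcome fields, and amendment cannot reach data nobody looked at.

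Three stronger readings are tempting and are not supported.

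- A reader might infer that the entry-error rate is the trial's measure of data quality under objective (ii). No section says so. Retention and completion rates and salivary validation are set out separately under Secondary outcomes.
- A reader might infer that the abstinence fields are likely to be badly wrong behind a passing rate. The large masking figures need a long form, few errors elsewhere and errors concentrated in those fields. The article gives no field count and no evidence of concentration.
- A reader might put one wrong entry at 7–10% of an arm's estimate. That is a relative figure resting on an assumed 10 to 15 abstinent women per arm; the absolute shift is about 1 percentage point.

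**Conclusion.** The point holds as a modest, inexpensive improvement, not as an error in the plan. On the natural reading of Data management, a passed check leaves entry errors in up to 80% of records undetected, and this includes the fields behind the future trial's primary outcome. A database-wide rate gives little assurance about those fields, but the size of any masking cannot be determined from the article. If entry errors are uniform and at or below 1%, about one wrong record per field would remain among 120 women. Each such entry shifts an arm's proportion by about 1 point, well inside the sampling error of a descriptive pilot without significance testing. The primary outcome, recruitment, and the sample-size figures are unaffected.

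**What to change.** In Data management, add that all entries for quit date, self-reported abstinence, saliva result, attendance and follow-up status are checked against source (questionnaire, laboratory report, attendance sheet). Keep the 20% sample with the 1% rule for all other data, and state the denominator of the error rate and what happens at exactly 1%. If the full protocol, codebook or salivary sample protocol already requires such checks, a sentence saying so is enough.

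The error rate found in the outcome fields before correction can be reported as a supplement under objective (ii). It does not replace the completion and salivary-validation assessments.

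The cost is extra checking time for the existing Research Fellow, at most about 1,940 values. The article gives no basis for converting this into hours.

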### Data analysis

The pilot data will be analysed on an intention-to-treat basis and will be mainly descriptive. A per protocol analysis will also be carried out. A separate statistical analysis plan will be produced. In brief, descriptive analyses will summarise baseline characteristics of women in each trial arm, eligibility rates, recruitment rates, participation, and attrition rates in preparation for a full trial. Subgroup analysis by GMS eligibility will be carried out. Elements of the RE-AIM (Reach, Effectiveness, Adoption, Implementation, and Maintenance) evaluation tool will provide a suitable framework to structure this analysis [34]. As this study is not powered to detect significant differences between groups, formal significance testing will not be carried out. The future trial primary outcome will be the comparison of the proportions of women between groups who self-report having quit smoking, corroborated by laboratory testing such as salivary cotinine at end of programme (12 weeks). The number of participants (%) experiencing cessation will be summarised between groups. The mean change scores (with 95% CIs) between groups on a range of questionnaires will be estimated, to assess whether these were in the expected direction of effect. An assessment of normality will be made on questionnaire scores, and parametric (means and SDs) and/or non-parametric estimates and variability (median/IQR) will be reported at baseline, 12 weeks, and 6 months. Descriptive analysis of secondary outcomes will summarise means and standard deviations for continuous outcome measures or numbers (%) for categorical data at baseline, 12 weeks, and 6 months.

Thematic analysis will be used to analyse qualitative data [35, 36]. Three members of the research team will independently read the transcripts and the diaries. Rigorous line-by-line coding will be applied, with a focus on experiential claims and concerns [37]. Coding will be carried out manually initially and a coding frame developed in Nvivo [37]. Patterns in the data will be clustered into a thematic structure to identify and categorise major themes and sub-themes. Data saturation will be achieved as conceptualised by inductive thematic saturation within the analyses, in relation to the (non-) emergence of new codes or themes [29]. Themes and sub-themes will be reviewed and refined to ensure a coherent pattern and to recode if necessary. Any differences in interpretation will be resolved through discussion. A fourth researcher with qualitative expertise, not involved in the trial, will review the coding frame and apply it to a subset of approximately 10% of the transcripts and two of the four diaries to reduce bias and ascertain the validity of the coding frame as an analytical tool [38]. A kappa coefficient will be calculated for inter-rater reliability. Fidelity to the intervention delivery will be analysed by the number and percentage of self-reported activities completed within each session. Completeness of session content will be noted within individual sessions and across the programme. Differences will be noted for completeness of core and optional session content.

Triangulation of the quantitative and qualitative processes will examine the interaction between context (e.g. group setting, recruitment strategy) and implemented strategies (e.g. training, lay advocate/statutory worker delivery) which led to certain outcomes (e.g. participant engagement, quitting /cutting down, participant satisfaction). The Consolidated Framework for Implementation Research (CIFR) which provides a menu of validated constructs that have been associated with effective implementation will provide a suitable theoretical framework to structure this analysis [39].

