#### Intervention delivery

Participants randomised to the intervention will receive 12 weekly behavioural support group sessions in a community setting, e.g. resource centre, and NRT dispensed by the community pharmacists. The group sessions are designed to enhance positive social support systems among peers. NRT is made available without cost to all intervention participants.

Each programme will be delivered in a local community facility by two trained CFs. Each session will last approximately 90 min. The CFs will make proactive personal contact both during and between sessions with participants using their own language and cultural style, and provide an opportunity to share testimonials and personal experiences. They will promote social support with delivery of emotional support (e.g. through demonstrating empathetic listening) among peers and will also carry out regular carbon monoxide (CO) monitoring.

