#### Control arm

Participants randomised to the control arm will receive a face-to-face individual smoking cessation programme offered by the HSE for men and women delivered by a Smoking Cessation Officer in a community setting [9]. This was chosen as a more suitable control intervention rather than the more readily accessible and widespread telephone and online service due to the difficulty in obtaining data on these services and similarity to the WCQ in terms of providing a face-to-face service. However, it is recognised that only a minority of women have access to this ‘Rolls Royce’ service due to lack of staff availability for service provision.

This programme encompasses, on average, 6–7 individual contacts offered in a primary care centre or hospital outpatient clinic. Sessions vary in duration and mode of delivery; however, the first of these is delivered face-to face (average session length between 30 and 45 min). Subsequent visits occur weekly or every 2 weeks and may be conducted by telephone.

Components of the behavioural support elements of the HSE programme include reinforcing motivation to quit and setting a quit date, building a repertoire of client coping strategies, providing information on the nature of tobacco addiction and withdrawal, undertaking regular carbon monoxide checks and giving feedback on progress, and planning ongoing coping mechanisms and support. Clients are informed about NRT and other smoking cessation pharmacotherapies and are advised to consult their general practitioner on these. HSE clients will obtain these free of charge if they are eligible for free General Medical Services (GMS).

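### The endpoint named as the future trial's primary outcome is defined inconsistently, both in the self-report criterion and in whether anabasine is required

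*Protocol article*

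**What the plan says.** Validated abstinence is described in four places in the protocol article.

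- **Objectives** refers to "biochemically validated abstinence from smoking (using salivary testing) at 12 weeks (end of programme) and 6 months (longer-term outcome") and names no marker.
- **Secondary outcomes, item (ii)** requires continuous abstinence under a cited standard, "at 12 weeks (primary outcome for a future DT) and at 6 months after their quit date", "corroborated by salivary cotinine and anabasine".
- **Secondary outcomes, data-collection paragraph** says "Salivary cotinine ± anabasine to biochemically validate self-reported smoking cessation will be recorded at week 12 and 6/12".
- **Data analysis** describes the future primary outcome as the proportion of women "who self-report having quit smoking, corroborated by laboratory testing such as salivary cotinine at end of programme (12 weeks").

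On access to NRT, Intervention delivery says "NRT is made available without cost to all intervention participants". Under Control arm, women are told about NRT and referred to their general practitioner, and "HSE clients will obtain these free of charge if they are eligible for free General Medical Services (GMS"). The eligibility criteria admit women already taking NRT, and current smokers who also use e-cigarettes, to either arm.

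**The concern.** Two parts of the definition move between sections. The first is the self-report criterion: continuous abstinence in one place, having quit in the other. A woman who returned to smoking after her quit date and then stopped again before week 12 could satisfy the second without satisfying the first. The second is the laboratory criterion: anabasine is required, optional or unnamed, depending on the sentence.

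The marker matters in this trial because cotinine is a nicotine metabolite and cannot by itself separate smoking from NRT or nicotine-containing e-cigarettes. Access to NRT differs between arms by design, and the first validation sample is taken as the 12-week programme ends, when some women may still be using NRT.

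No pilot hypothesis test is at stake, since none is planned. What is at stake is primary objectives (ii) and (iii): the quality and completeness of the validated outcome, and the design inputs (including the ICC) passed to the definitive trial. Even completeness depends on the wording, because a record with cotinine but no anabasine is complete under one sentence and incomplete under another.

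**Working it through.** **Side by side**

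| Place | Self-report criterion | Laboratory criterion |
|---|---|---|
| Secondary outcomes, item (ii) | Continuous abstinence, cited standard | Cotinine and anabasine |
| Secondary outcomes, data collection | Self-reported cessation | Cotinine, anabasine optional, no condition given |
| Data analysis | Having quit | Testing for which cotinine is the one example |

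The rows cannot all be followed literally. The article does not say when anabasine is added or how a cotinine-positive NRT user is classified.

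**Possible size of the effect**

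The plan states no abstinence rate and no NRT use at sampling, so it has no figure of its own to reproduce here. Its retention figure, 194 × 0.62 = 120.3 against a stated 120, does reproduce but plays no part below.

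Let p be true abstinence in an arm and u the share of its true abstainers using NRT at the sample. Assume every such woman is cotinine-positive. Under a cotinine-only rule, or a rule requiring both markers negative, the proportion counted abstinent is p × (1 − u). With equal true abstinence p in both arms, the difference seen (intervention minus control) is −p × (u_I − u_C). It is zero when use is equal, and it runs against the intervention only when u_I exceeds u_C.

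All values of p and u below are assumptions.

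| True abstinence, I v C | NRT use among abstainers, I v C | Counted abstinent, I v C | Difference seen (true) |
|---|---|---|---|
| 30% v 30% | 50% v 20% | 0.30 × 0.5 = 15% v 0.30 × 0.8 = 24% | −9 points (0) |
| 25% v 25% | 40% v 20% | 0.25 × 0.6 = 15% v 0.25 × 0.8 = 20% | −5 (0) |
| 20% v 20% | 40% v 40% | 0.20 × 0.6 = 12% v 12% | 0 (0) |
| 30% v 20% | 20% v 10% | 0.30 × 0.8 = 24% v 0.20 × 0.9 = 18% | +6 (+10) |
| 30% v 20% | 40% v 40% | 0.30 × 0.6 = 18% v 0.20 × 0.6 = 12% | +6 (+10) |
| 30% v 20% | 60% v 20% | 0.30 × 0.4 = 12% v 0.20 × 0.8 = 16% | −4 (+10) |
| any | 0% v 0% | unchanged | no bias |

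Equal use preserves a true null but still shrinks a real difference.

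To show what this could do to planning, take two-sided 5%, 80% power and no allowance for clustering. The usual formula is n per arm = [1.96 √(2p̄(1 − p̄)) + 0.842 √(p₁(1 − p₁) + p₂(1 − p₂))]² / (p₁ − p₂)².

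- 30% v 20%: (1.200 + 0.512)² / 0.10² gives 294.
- 24% v 18%: (1.129 + 0.483)² / 0.06² gives 723.

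If a marker that separates tobacco from NRT decides for every NRT user, u no longer enters and this bias disappears.

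**The case against.** The strongest reply is that no sentence sets a cotinine-only rule. Data analysis offers cotinine as an example, in a summary that defers to a separate statistical analysis plan. The outcome definition itself names anabasine, and the *±* sign can be read as adding anabasine where it is needed, for instance in NRT users. Nor does any sentence say that both markers must be negative. The operating rule may sit in the salivary sample protocol, which Data management cites but which is not shown. *Having quit* may be shorthand for the continuous abstinence defined earlier. Availability of NRT is not use, and control women may have substantial free access, because districts are selected partly on eligibility for free medical services. The pilot's own primary outcome is recruitment.

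Much of this stands. A reader might infer that the protocol validates by cotinine alone and that the future primary outcome will therefore be misclassified by arm. The documents do not support that: it would need a rule they do not impose, and a difference in NRT use at week 12 that they do not report. Cut-offs and laboratory procedure may properly be left to other documents, and their absence is not part of this point.

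The reply does not remove the inconsistency. If *±* means anabasine only for some women, it conflicts with item (ii), which attaches no condition, and the article does not say which women. An analysis plan written from this text would have to choose among the sentences.

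**Conclusion.** Wrong as written: an internal contradiction in the endpoint definition. The sections differ on the self-report criterion and on whether anabasine is required, for the outcome the pilot is meant to prepare for the definitive trial. That conclusion rests on the text alone.

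Bias between arms is conditional. It needs cotinine alone to be applied, or both markers to be required negative, and NRT use among abstainers at the sample to differ by arm. The access rules make higher use in the intervention arm plausible, but the documents do not establish it. Over the assumed cases, a true null is seen as anything from 0 to −9 points and a true +10 as anything from +10 (no use) to −4. These figures illustrate scale and are not estimates for this trial. The consequence falls on the cessation rates, ICC and sample size carried forward, not on any test in the pilot.

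**What to change.** Use one definition in Secondary outcomes and in Data analysis: self-reported continuous abstinence per the cited standard, at 12 weeks and 6 months, biochemically verified as follows.

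- Record use of NRT and e-cigarettes at each saliva sample.
- For women who report such use, anabasine decides.
- For all others, cotinine decides.

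Replace *and*, *±* and *such as* to match, and check that the salivary sample protocol and the statistical analysis plan say the same.

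Anabasine need not be run on every sample. The cost is that it becomes mandatory for women reporting nicotine-product use, and that one question is added at sampling. The assay is already planned, so the extra laboratory cost should be small, though the documents give no price. The rule also relies on women reporting their product use accurately.

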### Randomisation and allocation concealment

Four matched pairs of districts (eight clusters) will be randomised with each matched pair of clusters randomised to intervention or controls in a 1:1 allocation ratio. The randomisation will follow a pragmatic approach whereby paired districts ready for the intervention will be randomised first, followed by the next available matched pair; this accounts for temporal changes and will provide a balanced design.

The randomisation will be conducted remotely by the Wellcome Trust Clinical Research Facility (CRF) independent of the Trial Management Team, who will develop a standard operating procedure for this process. The code for each matched pair of districts will be concealed and securely stored by the Wellcome CRF at St. James’s Hospital. It will be revealed to the WCQ2 trial team once sufficient numbers have been recruited (or by agreement with the Trial Management Group (TMG) if recruitment is insufficient prior to intervention delivery). Practitioners will be informed of the area in which they will deliver their programme by the research team, and participants will be informed of their allocation by the practitioners. Figure 1 displays an overview of cluster randomisation process.

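### Questionnaire scores are compared between arms by mean change, where a baseline-adjusted comparison would be more precise and would not move with chance baseline imbalance

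*Protocol article*

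**What the plan says.** The Data analysis section describes the general approach as follows: "The pilot data will be analysed on an intention-to-treat basis and will be mainly descriptive". For the questionnaires it then names a between-arm estimate: "The mean change scores (with 95% CIs) between groups on a range of questionnaires will be estimated". It also gives the purpose: "to assess whether these were in the expected direction of effect". This is the only place in the section where a confidence interval is mentioned. Cessation and the other secondary outcomes are to be summarised by numbers and percentages, or by means and SDs at each time point.

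Testing is ruled out: "As this study is not powered to detect significant differences between groups, formal significance testing will not be carried out". Further detail is deferred: "A separate statistical analysis plan will be produced".

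Under Secondary outcomes, quality of life (SF-12 version 2) and health status are recorded at week 1, so baseline scores exist. Nowhere does the article mention adjusting a follow-up comparison for them.

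On the design, "Four matched pairs of districts (eight clusters) will be randomised". On numbers, the Sample size section says that "if 194 women (97 per arm) are recruited into the study, 120 women are predicted to be in this pilot study by 12 weeks".

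**The concern.** Subtracting the baseline score assumes that a baseline difference between arms would carry through in full to follow-up. Unless baseline and follow-up are perfectly correlated it does not, because scores regress towards the mean. An arm that happens to start higher will tend to show a smaller rise or a larger fall, whatever the treatment does. Subtraction also adds the noise of the baseline measurement to that of the follow-up measurement.

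The protocol says what these estimates are for: judging whether effects run in the expected direction. A chance baseline difference acts directly on that reading, and with eight clusters such differences are easily large enough to notice. What is at stake is the precision and the sign of the questionnaire comparisons, and nothing beyond them.

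**Working it through.** **Inputs from the protocol article**
- Recruited: 194 women, 97 per arm, in 8 clusters (Sample size; Randomisation and allocation concealment).
- Retention at 12 weeks: 62%, from 83/133 (Sample size).
- Baseline quality of life and health status at week 1 (Secondary outcomes).

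**Assumptions, because the article gives no figure**
- Correlation r between baseline and follow-up score: 0.3 to 0.8.
- ICC of the questionnaire scores: 0 to 0.05.
- Equal score variance at both times, and equal retention in the two arms.

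**1. The plan's own figure.** 194 × 0.62 = 120.3, which reproduces the stated 120 (194 × 83/133 gives 121.1). A change score exists only for women who are followed up, so the relevant numbers are about 120/2 = 60 per arm and 120/8 = 15 per cluster, not 97 per arm.

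**2. Size of a chance baseline difference, in SD units.** SD of the difference = √(2 × DE / 60), with DE = 1 + (15 − 1) × ICC.
- ICC 0: DE = 1.00, √(2/60) = 0.18
- ICC 0.01: DE = 1.14, √(2.28/60) = 0.19
- ICC 0.05: DE = 1.70, √(3.40/60) = 0.24

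A difference of 0.2 SD is therefore about one standard deviation of chance variation. The formula takes no credit for matching.

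**3. Precision and shift.** Per woman, in units of the score variance, the change score has variance 2(1 − r) and the baseline-adjusted follow-up score 1 − r². The ratio is 2(1 − r)/(1 − r²) = 2/(1 + r), and the CI width ratio is its square root. The 95% half-width is 1.96 × √(2 × variance / 60), ignoring clustering. A baseline difference d shifts the expected change-score estimate by −(1 − r)d; the adjusted estimate does not shift.

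| r | Variance ratio | Half-width, change | Half-width, adjusted | Change CI wider by | Shift for d = 0.2 SD |
|---|---|---|---|---|---|
| 0.3 | 1.54 | 0.423 | 0.341 | 24% | −0.14 SD |
| 0.5 | 1.33 | 0.358 | 0.310 | 15% | −0.10 SD |
| 0.7 | 1.18 | 0.277 | 0.256 | 8.5% | −0.06 SD |
| 0.8 | 1.11 | 0.226 | 0.215 | 5% | −0.04 SD |

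**4. Check with clustering.** A simulation of 8 clusters of 15 women (4,000 runs per setting; ICC 0, 0.02 and 0.05; the same correlation at cluster and individual level; no matching) gave standard-error ratios of 1.24–1.26, 1.15, 1.07–1.09 and 1.05 at the four values of r. The slope of the change-score estimate on the baseline difference was about −0.7, −0.5, −0.3 and −0.2. For the adjusted estimate it was close to 0. The simple formulae therefore hold up under clustering.

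**5. What this means for reading direction.** As an illustration, take a true effect of 0.2 SD, r = 0.5, 60 per arm, and ignore clustering. The standard error is √(2 × 1.00/60) = 0.183 for the change score and √(2 × 0.75/60) = 0.158 for the adjusted estimate. The chance of an estimate with the wrong sign is Φ(−0.2/0.183), about 14%, against Φ(−0.2/0.158), about 10%.

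**The case against.** **The choice belongs to the SAP.** The article condenses, calls the analysis mainly descriptive and promises a separate plan. It does not exclude a baseline covariate, and change regressed on arm and baseline gives the same arm effect as follow-up regressed on arm and baseline. It is true that the unseen plan could add the covariate, and a reader should not infer that adjustment is ruled out. But the article is not silent here: it names the between-arm estimate, and as written that is mean change. The point concerns a stated method, not a missing detail.

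**The consequences are small.** A reader might infer that overstated variability will carry into the size of the definitive trial. The documents do not support that. The Sample size section and the third primary objective rest the definitive trial on the ICC, recruitment and attrition. Its primary outcome is a proportion, validated abstinence. Progression uses ADePT and PRECIS-2. Questionnaire SDs have no stated role in any of these. Baseline means are also to be reported, so an imbalance would be visible. This part of the objection stands in full and sets the weight of the point.

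**The change score is not biased.** Averaged over randomisations this is right, and a correctly computed interval already covers the baseline variation. At r = 0.5 a shift of 0.10 SD is well inside a half-width of 0.36 SD. What remains is a loss of precision, and an estimate that is predictably off once the observed imbalance is known.

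**The imbalance may be smaller than shown.** Districts are matched on population size and deprivation, which may reduce it. They are not matched on questionnaire scores, so the gain is unknown.

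**Adjustment is not free with eight clusters.** In a cluster-level analysis, adding matched pair takes the degrees of freedom from 6 to 3 and the t critical value from 2.45 to 3.18. A cluster-level baseline covariate would leave 2 (4.30). That could cancel the gain, so the adjustment should be made at individual level and the pair term should not be part of the requirement.

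**Conclusion.** The point holds, with limited weight. The protocol's stated between-arm estimate for the questionnaires is less precise than one that uses the same data with the baseline score as a covariate, and it moves with chance baseline imbalance. The CIs are about 24% to 5% wider, and an ordinary imbalance of 0.2 SD shifts the estimate by 0.14 to 0.04 SD.

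These sizes rest on an assumed r of 0.3 to 0.8, equal variances at the two times, and about 60 women per arm. The article expects lower retention under usual care. Unequal arms would widen both intervals but leave the variance ratio 2/(1 + r) unchanged. The direction of both effects holds for any r below 1.

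The scope is confined to secondary, descriptive comparisons made without significance tests.

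**What to change.** In Data analysis, replace the change-score sentence with text such as: *The between-arm difference in follow-up questionnaire score, adjusted at individual level for the baseline score and allowing for clustering by district with a small-sample method, will be estimated with a 95% CI. No significance test will be made. Raw mean change will be reported by arm as description.*

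The cost is one sentence, a few lines of code and one more model term. No extra participants or measurements are needed, because the week 1 scores are already planned.

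Two further choices are optional and can be left to the SAP. One is adjustment for matched pair, which uses scarce degrees of freedom. The other is the timing of the baseline score: the article places baseline demographic data at consent and the questionnaires at week 1, so a score taken before allocation is revealed might need a change of schedule.
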